### Data management

All data will be handled in accordance with the 2018 Data Protection Act. Hard copies of CRFs linking patient‐identifiable information to their unique study ID and study data will be kept securely by recruiting sites and only accessible to a small number of defined people involved in the study. Anonymized data will be entered into MACRO [45]—a secure electronic data collection system, backed up to a central server—which will be developed and maintained by North Wales Organisation for Randomised Trials in Health (NWORTH) Clinical Trials Unit (CTU). MACRO has inbuilt controls to minimize data entry errors and data can be entered, reviewed and amended whilst generating an audit log. Data management is fully described in the COLO‐DETECT Data Management Plan. Data monitoring and source data verification will be conducted by the sponsor, independent of investigators, after the first 20 participants recruited at each study site and 6 monthly thereafter. All study paper and electronic data and documentation will be stored for 15 years after study completion as per sponsor and CTU policy.

### Data analysis

A full statistical analysis plan will be developed prior to analysis commencing. Statistical analysis will be performed by NWORTH CTU. The trial statistician and chief investigator will remain blinded throughout the trial and data analysis. The primary outcome, MAP in GGC versus SC, will be analysed using an ANOVA, using the randomization stratification variables as factors. The key secondary outcome, ADR, will be analysed using logistic regression, forcing trial arm into the model and including randomization stratification variables as factors. This approach will also be used to analyse the detection rate of SSPs, advanced adenomas and cancer, as well as caecal intubation rate, and effects on future colonoscopy workload. Subgroup analyses will be conducted on colonoscopist type (i.e., non‐BCSP accredited vs. BCSP accredited) and indication for colonoscopy (screening vs. symptomatic).

Whether group difference (GGC vs. SC) exists for the nature, morphology, and distribution of polyps found in the colorectum, will be analysed using a multinomial logistic regression; polyp size will be analysed using an ANOVA, as will whether group difference (GGC vs. SC) exists for withdrawal times (in procedures where no polyps were found), insertion time to the caecum (or limit of examination where the caecum is not reached), MPP and patient experience (measured using the Newcastle ENDOPREM™).

To identify changes in MAP and ADR over the time of the study (which might occur due to the trial progression effect [46]), detection rates for the first 20% of participants will be compared with those for the last 20% of participants for each colonoscopist, using repeated measures *t* tests and visual plots. Parallel data on reported detection rates amongst a selection of colonoscopists from the same units but not participating in the study will be compared with the measures obtained in the SC group.

Analyses will be performed using a 5% significance level (two‐sided) and effect size estimates will be presented with 95% confidence intervals. All analyses will be completed on an intention‐to‐treat and per protocol basis and will include all randomized patients. We will additionally undertake sensitivity analysis limiting analysis to patients with complete colonoscopy. Should substantial data be found to be missing for a measure or variable (i.e., ≥5%), predictors of missingness will be investigated using regression modelling. Multiple imputation may also be employed to address missing values where appropriate.

A ‘within study’ economic evaluation will be conducted to determine cost effectiveness of GGC versus SC from the perspective of the NHS. It will be based upon the costs of randomized interventions received and on use of subsequent care and services. Use of resources will be collected including duration of procedure, resource use and associated staff costs (including grade of staff), any additional treatment prescribed (e.g., analgesics), appointments missed, any hospital inpatient stays, and any AEs and associated treatment. The EQ‐5D‐5L will provide utility information. Incremental cost effectiveness ratio (cost per quality‐adjusted life‐year) will be estimated with robustness of results evaluated in a sensitivity analysis. The incremental cost effectiveness ratio will be compared against thresholds used to establish value for money in the NHS (currently in the region of £20 000–£30 000 per quality‐adjusted life‐year).

Economic modelling approaches will be used to explore longer‐term economic consequences and patient benefits (including effects on CRC) of GI Genius™, across a lifetime horizon.

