### COLO‐DETECT

COLO‐DETECT is a parallel arm, multi‐centre (Box 1) randomized controlled trial that will compare polyp detection during GI Genius™‐assisted colonoscopy (GGC) to detection during standard colonoscopy (SC), in the context of routine colonoscopy practice in the UK. This includes patients referred for reason of gastrointestinal symptoms or requiring surveillance colonoscopy (together henceforth referred to as the ‘symptomatic population’) or as part of the national Bowel Cancer Screening Programme (BCSP, the ‘screening population’). Whilst tandem colonoscopy studies have been used elsewhere in endoscopy studies, and require smaller sample sizes to demonstrate effect, it was felt that a parallel arm design was both more pragmatic and reflective of clinical practice and thus more in keeping with the ethos of the study, especially as the sample size required to demonstrate a significant difference in detection using a parallel arm design was not deemed excessive (see the section Sample size, below).

BOX 1List of COLO‐DETECT study sites (subject to potential new sites)**Table jats-table-wrap-1:** 

South Tyneside and Sunderland NHS Foundation Trust (Sponsor site), North Tees and Hartlepool Hospitals NHS Foundation Trust, South Tees Hospitals NHS Foundation Trust, Kettering General Hospital NHS Foundation Trust, University Hospitals of Morecambe Bay NHS Foundation Trust, Bolton NHS Foundation Trust, Royal Wolverhampton NHS Trust, Newcastle‐upon‐Tyne Hospitals NHS Foundation Trust, Northumbria Healthcare NHS Foundation Trust
NHS, National Health Service.

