Upon attending for colonoscopy, consent will be confirmed in writing and participants will complete the EQ‐5D‐5L health‐related quality of life questionnaire [40]. Participants will be randomized by recruiting staff 1:1 to GGC or SC [41] using a secure web‐based platform. Randomization will be stratified by age category (<60 years, between 60 and <74 years, ≥74 years), sex, study site and referral category (symptomatic or screening population). In the event of randomization platform unavailability, a coin toss will be used.

Standard colonoscopy represents standard care for colonoscopy at each study site. GGC incorporates all elements of SC and differs only in that the GI Genius™ will be turned on and activated for at least the whole of the inspection phase of withdrawal, although the investigators recommend to participating colonoscopists that the GI Genius™ is activated prior to the procedure. Procedural data will be recorded onto a Case Report Form (CRF). Post‐procedure, participants in both arms will undergo standard post‐colonoscopy care and discharge procedures for each site.

Prior to discharge participants will be given a patient experience questionnaire (the validated Newcastle ENDOPREM™ [37]) and a second iteration of the EQ‐5D‐5L to complete and return in a pre‐paid envelope. Follow‐up will cease upon completion of a post‐procedure review between days 14 and 21. This may include accessing medical records (including endoscopy reports and histology) and a telephone call to assess whether any adverse events (AEs) or serious adverse events (SAEs) have occurred. No further contact will be required for study participation, although participants will be asked to consent to long‐term (up to 5 years) passive follow‐up of health outcomes through endoscopy data, medical records and national databases such as the National Cancer Registry Database, Hospital Episode Statistics data, National Endoscopy Database [42] and link to the CORECT‐R data repository [43]. Where data are currently anonymized participant consent will be sought to link data when this becomes possible. Present and future clinical care will be unaffected by study participation.

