### Data collection

Baseline data (age, sex, indication for colonoscopy, colonoscopist study ID and BCSP accreditation status) will be recorded into a CRF pre‐procedure along with trial arm. Post‐procedure, the following data will be recorded:
medications usedvideo processor manufactureruse of a mucosal visualization deviceprocedure timings (start/end times, withdrawal commencement and withdrawal time—in minutes)furthest extent reached (and reason caecum not reached, if relevant)whether retroflexion was performedquality of bowel preparation (using standard JAG classifications)nurse‐assessed and colonoscopist‐assessed patient comfort scores (using the modified Gloucester comfort score)pathology identified (including polyps, cancer, inflammatory bowel disease etc.)whether any polyps were detected on insertion or withdrawalpolyp location, size, morphology, removal method and retrieval statushistology of any biopsies or polyps retrievedoccurrence of any AEs or SAEsanticipated interval to any subsequent surveillance colonoscopy (based solely on the application of the latest British Society for Gastroenterology guidelines [38] to recorded endoscopic findings and histology)whether GI Genius™ was deactivated or suffered a technical malfunction during the colonoscopy (relevant for planned process evaluation)

If required, participants will receive the following: a verbal reminder (by telephone) from a member of the research team to complete and return their post‐procedure questionnaires; with a written reminder (and another copy of the questionnaire) sent 4 weeks post‐procedure.

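### The MAP and ADR models adjust for banded age and a two-level referral category although finer baseline values are recorded or probably recorded; a small, free gain in efficiency is left unused.

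*Protocol article*

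**What the plan says.** In the protocol article, Data analysis section, MAP "will be analysed using an ANOVA, using the randomization stratification variables as factors". ADR is analysed by logistic regression, "forcing trial arm into the model and including randomization stratification variables as factors".

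The Study process section defines those variables. Randomisation is "stratified by age category (<60 years, between 60 and <74 years, ≥74 years), sex", and also by "study site and referral category (symptomatic or screening population"). The introduction, under the heading COLO-DETECT, defines the symptomatic population as "patients referred for reason of gastrointestinal symptoms or requiring surveillance colonoscopy", so the two referral routes share one factor level.

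The Data collection section states: "Baseline data (age, sex, indication for colonoscopy, colonoscopist study ID and BCSP accreditation status) will be recorded" before the procedure. Box 4 lists clinical symptoms, surveillance and the screening programme (BCSP) as three separate referral routes. When the Data analysis section names the subgroup variable it uses two levels: "indication for colonoscopy (screening vs. symptomatic"). A full statistical analysis plan is to be written before analysis starts.

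**The concern.** Surveillance patients enter because of an earlier colonoscopy or bowel pathology. There is no reason to presume that they have the same expected adenoma yield as patients referred with new symptoms. The models give the two groups a common referral term, so within a given age band, sex and site they share one fitted mean. Age is likewise held constant within each of three wide bands.

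If age and route of referral predict adenoma yield, the variation they explain within those coarse levels stays in the residual. Both quantities are fixed before the procedure. A three-level indication also nests inside the two-level stratifier, so using it still respects the randomisation. What is at stake is a little efficiency in the primary and key secondary comparisons, available without recruiting anyone.

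**Working it through.** **1. Reproduce the stated sample size.** Inputs from the Sample size section: control ADR 27.6%, difference 7 points (so 34.6%), two-sided alpha 0.05, power 90%, attrition 10%.

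Unpooled two-proportion formula, per arm:

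n = (1.960 + 1.282)² × [0.276 × 0.724 + 0.346 × 0.654] / 0.07²
= 10.507 × (0.1998 + 0.2263) / 0.0049 = 913.7, so 914 per arm and 1828 in total.

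Attrition: 1828 / 0.9 = 2031.1, or 2032 as an even number. Both stated figures reproduce. The pooled-variance version gives 917 per arm (1834).

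Power at 914 per arm with the pooled-variance test, using the mean proportion 0.311:

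Φ{[0.07√914 − 1.960√(2 × 0.311 × 0.689)] / √0.4261} = Φ(1.276) = 0.899.

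The calculation contains no covariates.

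**2. Assumptions needed for the gain.** The documents give neither the prognostic strength of age or surveillance nor the surveillance share. The assumed ranges were:

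- odds ratio per 10 years of age: 1.2 to 1.6
- odds ratio, surveillance against symptoms: 1.0 to 3.0
- surveillance share of the non-screening group: 20% to 40%
- screening 40% of the sample (from the Sample size section), screening odds ratio 2.5, sex odds ratio 1.6
- overall ADR 31.1% (midpoint of 27.6% and 34.6%)
- overdispersed adenoma counts with mean 0.6
- age spread evenly over 56 to 75 years in screening patients; mean 60, SD 14 otherwise

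Each scenario had 400,000 simulated patients. The coarse model held age bands, two-level referral and sex. The fine model added linear and quadratic age and a surveillance indicator. Site was not simulated.

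**3. Residual variance.** Reduction v = 1 − (1 − R²fine)/(1 − R²coarse), from linear models for both outcomes.

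| Scenario (age OR, surveillance OR, share) | ADR R², coarse → fine | v | MAP R², coarse → fine | v |
|---|---|---|---|---|
| 1.2, 1.0, 20% | 0.0670 → 0.0684 | 0.15% | 0.0674 → 0.0683 | 0.1% |
| 1.6, 1.0, 20% | 0.0973 → 0.1055 | 0.9% | 0.0816 → 0.0880 | 0.7% |
| 1.4, 2.0, 40% | 0.0556 → 0.0706 | 1.6% | 0.0528 → 0.0658 | 1.4% |
| 1.6, 3.0, 40% | 0.0584 → 0.0931 | 3.7% | 0.0509 → 0.0842 | 3.5% |

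Check of the last row for ADR: 1 − 0.9069/0.9416 = 0.037. Across all scenarios v runs from about 0.1% to 3.7%.

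**4. Translate.**

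- Standard error on the linear scale: at v = 3.7%, √(1 − 0.037) = 0.981, or 1.9% smaller. At v = 0.1% the change is negligible.
- Participants: 0.0368 × 1828 = 67 at the top; 0.0009 × 1828 = 2 at the bottom.
- ADR power: replace 914 by 914/(1 − v). At v = 0.0368 this is 949, giving Φ(1.338) = 0.9095. At v = 0.0015 it is 0.8995. The largest rise is 0.9095 − 0.8991, about one percentage point.

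**5. What the ADR figures mean.** They are on a linear (risk difference) scale. In the planned logistic model, adding prognostic covariates does not shrink the standard error of the log odds ratio. The conditional odds ratio moves further from 1, and power rises that way. A gain in precision as such applies to the MAP difference and to a standardised risk difference.

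**The case against.** The strongest case against is that nothing here is wrong. Adjusting for the stratification variables is standard and valid, a fuller analysis plan is promised, and the ADR wording does not exclude further covariates. The validity point stands. But the covariates of both main models are stated in the article, not left open, so a plan that follows it will inherit the coarse coding.

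Four stronger readings are tempting, and the documents do not support them.

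- **That the coarse adjustment costs the trial its power.** It does not: step 1 shows that 1828 was obtained with no covariates at all.
- **That the gain is larger.** Suppose one compares only three-level with two-level indication and assumes surveillance MAP of 0.5 to 1.0 against 0.15 to 0.20 for symptoms. The reductions are then 1–5% for MAP and 1–6% for ADR, or about 20–120 of 2032 participants. That leaves out the age bands and sex already in the model, admits no scenario with little difference between the groups, and counts against the number recruited instead of the 1828 needed.
- **That the trial certainly holds a three-level indication.** The Data collection section names indication without its levels, and the Data analysis section uses two. Three-level capture is a fair inference from Box 4, but only an inference. Age is less doubtful, since it is listed as age and not as a category.
- **That finer adjustment would stop the symptomatic subgroup from mixing two populations.** A main-effect term does not change whose treatment effect is averaged. Only a split would, and on a 20–40% share the surveillance part is about 220 to 440 patients (0.6 × 1828 × 0.2 to 0.4). The protocol defines the pooled group deliberately and sets its meaningful differences for it.

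**Conclusion.** The point holds as a minor, free improvement. The planned models are valid, but they use coarser versions of age and, probably, indication than the trial records. Under the assumed ranges the finer covariates reduce residual variance by about 0.1% to 3.7%, equivalent to roughly 2 to 67 of 1828 participants, and ADR power rises by no more than about one point. If surveillance and symptomatic patients carry the same risk, the gain comes from age alone and is at most about 0.9% of variance. These sizes rest wholly on assumed prognostic strengths and surveillance share. The part concerning indication also depends on its being captured at three levels. Severity is low.

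**What to change.** Before analysis begins, pre-specify in the MAP and ADR models:

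1. Age as a continuous covariate with a non-linear term. Keeping the bands as well is harmless, and is what the figures above assume.
2. If the case report form captures it, indication at three levels (symptoms, surveillance, BCSP) in place of the two-level referral category. If it does not, keep the two-level factor.
3. Sex and site as now planned.

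For ADR, report a standardised risk difference with its confidence interval beside the adjusted odds ratio, and state that the odds ratio is conditional on the listed covariates. Any presentation of the symptomatic result split by symptoms and surveillance should be labelled descriptive.

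The cost is model wording, plus a check of how indication is coded. If three levels are recorded, no new data are needed, and the sample size is unaffected either way.

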Primary objective: to compare mean number of adenomas per procedure (MAP) between GGC and SC Key secondary objective: to compare ADR between GGC and SC Other secondary objectives are*: to determine whether there is a difference in MAP and/or ADR between GGC and SC within each of the screening and symptomatic populations to determine whether there is a difference in mean polyps per procedure (MPP) or polyp detection rate (PDR) between GGC and SC to ascertain the nature and distribution of all polyps in the colorectum, including location, size and morphology, comparing GGC and SC to ascertain if there is a difference in the detection rate of sessile serrated polyps (SSP) between GGC and SC to ascertain if there is a difference in cancer detection rate between GGC and SC (this includes polyps removed at colonoscopy and subsequently found to be cancerous, and lesions felt to be cancerous at the time of colonoscopy) to determine whether there is a difference in advanced adenoma detection rate (AADR) between GGC and SC to determine if there is a difference in caecal intubation rate, insertion time to caecum, total procedure time, withdrawal time in the absence of polyps, and colonoscopist‐assessed and nurse‐assessed patient comfort scores between GGC and SC to determine if there is a difference in patient experience between GGC and SC, utilizing a validated patient‐reported experience measure [37] to identify any projected difference in future post‐polypectomy surveillance colonoscopy workload, according to the application of national guidelines [38] to participant‐level polyp data comparing GGC and SC to compare MAP and ADR between BCSP and non‐BCSP colonoscopists, comparing GGC and SC to compare MAP and ADR between colonoscopists of differing experience levels, as indicated by lifetime procedure numbers and average annual numbers of procedures performed in the last 3 years to compare MAP and ADR for the first 20% of study participants scoped by each colonoscopist with the last 20% of participants to identify any changes in MAP or ADR throughout the study to compare baseline MAP and ADR of each colonoscopist (6 months pre‐study) with that colonoscopist's MAP and ADR during the study in the SC arm (to assess for a contamination effect) and for 6 months post‐study (to assess for dependence upon GI Genius™) to collect contemporaneous data on MAP and ADR for colonoscopists not taking part in the study to follow up patients to identify future outcomes related to colorectal polyps or CRC In addition, further secondary objectives are: to collect data that will allow subsequent health economic evaluation to determine the cost effectiveness of GGC compared with SC to undertake a process evaluation including investigation of user experience of GI Genius™ (see Box 3)

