## DISCUSSION

Artificial‐intelligence‐powered CADe is an emerging and exciting field in gastrointestinal endoscopy, with the hope it will produce a step‐change in lesion detection. It follows in the footsteps of improving endoscopy technology and devices with a clear evidence base and moves from seeking further gains in mucosal visibility to focusing on improving lesion detection on visible mucosa. Internationally, many artificial‐intelligence‐based detection systems have been developed and validated, with some initial evidence from their use in clinical practice [31, 32, 33, 35, 49]. Like all new interventions and technologies, though, robust, large‐scale clinical trials set in routine practice are required to demonstrate clinical relevance and to inform changes in practice. However, adoption of novel technology into healthcare systems does not occur solely on the basis of clinical effectiveness, assessment of which should be accompanied by economic evaluation to facilitate informed commissioning and purchasing decisions.

COLO‐DETECT will help address the evidence gap by recruiting over 2000 participants (to allow for up to 10% incomplete colonoscopies) across multiple sites, including specialist and non‐specialist centres, increasing the generalizability of results. It will have the power to detect clinically significant differences in lesion detection, should they exist, by measuring any differences using MAP as primary outcome and ADR as key secondary outcome. MAP (also referred to as adenomas per colonoscopy) is an alternative measure of lesion detection that has been used in polyposis syndrome trials given the high number of polyps in this patient group. It has also been proposed as the most important marker for polyp prevention trials [50], as it gives an indication of the overall number of adenomas present, whereas ADR is only binary, that is, ≥1 or none. The use of MAP avoids the ‘one and done’ phenomenon and is coherent with the ambition to clear a colon of potentially cancerous lesions [15]. This principle is as applicable to colonoscopy in routine practice as it is to polyp prevention trials, meaning that MAP may be a more appropriate outcome measure in CADe studies than ADR [51]. However, ADR has historically been used as the main marker of colonoscopy quality. COLO‐DETECT will thus measure ADR and MAP.

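### The tests named for polyp type, morphology, location and size make no allowance for several polyps per participant, and they compare only detected polyps

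*Protocol article*

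**What the plan says.** Box 2 of the protocol article (Study objectives) lists a secondary objective "to ascertain the nature and distribution of all polyps in the colorectum, including location, size and morphology, comparing GGC and SC". The Data analysis section fixes the methods for it: arm differences in the nature, morphology and distribution of the polyps found "will be analysed using a multinomial logistic regression; polyp size will be analysed using an ANOVA". It names no unit of analysis, patient random effect or robust variance for these outcomes.

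Four other places bear on the point:

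- **Data collection:** location, size, morphology, removal method and retrieval status are recorded for each polyp.
- **Study process:** "Participants will be randomized by recruiting staff 1:1 to GGC or SC", so the participant is the unit of randomisation.
- **Discussion:** mean adenomas per procedure (MAP) is preferred because "it gives an indication of the overall number of adenomas present, whereas ADR is only binary". The trial therefore expects more than one lesion in some patients.
- **Data analysis, general rules:** tests are two-sided at 5%, and "All analyses will be completed on an intention‐to‐treat and per protocol basis and will include all randomized patients".

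The article also says that a full statistical analysis plan (SAP) will be written before analysis starts. That plan is not available here.

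**The concern.** There are two separate problems.

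**Clustering.** A patient with a flat polyp in the caecum and a pedunculated one in the sigmoid has no single morphology or location category. A multinomial model for these outcomes therefore runs naturally on polyps. In its ordinary form it treats polyps from one patient as independent. If polyps within a patient resemble each other, the standard errors are too small and the 5% test rejects too often.

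**Conditioning on detection.** The analysed set is the polyps found, which is determined after randomisation and is what the device is meant to change. The Introduction says that small, flat adenomas make up a disproportionate share of missed lesions. If the device recovers some of them, mean size falls and the morphology mix shifts in the GI Genius-assisted (GGC) arm, even when every large lesion is still found. A reader could mistake this for poorer detection of large lesions. Clustered standard errors do not cure it.

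At stake is a secondary objective that helps to describe what any extra detection consists of.

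**Working it through.** **The plan's own figure.** The article states no figure for the polyp-feature analyses. Its only sample size is for the adenoma detection rate (ADR), 27.6% against 34.6% with 90% power:

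n per arm = (1.960 + 1.282)² × (0.276×0.724 + 0.346×0.654) / 0.07² = 913.7, so 914 per arm and 1828 in total; 1828/0.90 = 2031.1, close to the stated 2032 (rounded up).

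This reproduces. It has no bearing on the point beyond supplying the 914 per arm used in the simulation below.

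**Effect of ignoring clustering.** The article gives neither polyps per patient nor a within-patient ICC, so both are assumed and varied. Let m be the size-weighted mean number of polyps per patient with at least one polyp (Σc²/Σc over patients with c polyps).

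- Design effect: DEFF = 1 + (m − 1) × ICC
- Naive SE / true SE = 1/√DEFF
- True two-sided type I error = 2 × [1 − Φ(1.96/√DEFF)]

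Lower end, m = 2 and ICC 0.05: DEFF = 1.05, SE ratio 0.976, 1.96/1.025 = 1.913, type I error 5.6%.

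Upper end, m = 4 and ICC 0.3: DEFF = 1.9, SE ratio 0.725, 1.96/1.378 = 1.422, type I error 15.5%.

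| m | ICC 0.05 | ICC 0.1 | ICC 0.2 | ICC 0.3 |
|---|---|---|---|---|
| 2 | 5.6% | 6.2% | 7.4% | 8.6% |
| 3 | 6.2% | 7.4% | 9.8% | 12.1% |
| 4 | 6.8% | 8.6% | 12.1% | 15.5% |

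At ICC 0, DEFF = 1 and there is no inflation.

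**Check by simulation.** The set-up was 914 patients per arm, no true arm effect, negative binomial polyp counts (mean 1.0, shape 0.6, giving m of about 3.7), a continuous polyp feature, and 1500 replicates.

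| ICC | Two-group test on polyps | Patient-clustered variance |
|---|---|---|
| 0 | 4.1% | 4.5% |
| 0.1 | 8.0% | 5.2% |
| 0.2 | 11.7% | 5.3% |
| 0.3 | 14.1% | 4.9% |

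The simulation agrees with the formula, and clustering the variance by patient restores the nominal level. It covers a size-type comparison. The multinomial models were not simulated.

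**Effect of conditioning on detection.** Assume that standard colonoscopy finds polyps of mean 6 mm, and that GGC finds the same polyps plus 20% more with mean 3 mm. Mean size in the GGC arm is then (6 + 0.2×3)/1.2 = 5.5 mm. It falls by 0.5 mm although nothing was missed. With 10% or 30% extra polyps the mean is 5.7 or 5.3 mm. The sizes are illustrative.

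**The case against.** A reader might infer that the plan treats each polyp as an independent observation. The article does not say so. A multinomial regression with patient-clustered variance is still a multinomial regression. For size, the same sentence applies ANOVA to per-patient quantities such as withdrawal time and polyps per procedure, so a per-patient mean or largest size would fit the text. The inference is strong for the multinomial model and weak for size.

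A reader might also infer that false arm differences are likely. The figures do not support that. They rest on assumed inputs, they are small at the low end (6.2% at m = 2 and ICC 0.1), and even at 15.5% most null tests are not significant.

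The unit and the variance estimator are often left to the SAP, which may settle both. Describing what each arm found is also a legitimate question, and the article does not claim a causal reading of it. Finally, advanced adenoma, sessile serrated polyp and cancer detection rates and surveillance workload address clinical relevance separately.

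These objections limit the size of the point but do not remove it. The article goes beyond silence: it names the model families and restricts the multinomial comparison to polyps found, and an SAP that followed it literally would inherit both problems. A comparison of polyp features also cannot include all randomised patients, as the general rule requires, because patients without polyps have no value.

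**Conclusion.** The point holds in limited form. The named tests carry no stated allowance for several polyps per participant. If polyps are analysed as independent and the within-patient correlation is positive, standard errors are too small. The type I error is then about 5.6% to 15.5% for m = 2 to 4 and ICC 0.05 to 0.3, with the true SE about 2% to 38% larger than the naive one (√1.05 = 1.025; √1.9 = 1.378). Both inputs are assumptions, so this is a range of possibilities and not an expected error rate.

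For the multinomial analyses, conditioning on detection follows from the text without any assumption about the unit. For size it applies equally, since size exists only for polyps that were found.

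It would be wrong to carry the point over to the main results. MAP, ADR, polyps per procedure, and the polyp, serrated-polyp and advanced-adenoma detection rates are defined per procedure and are unaffected by it.

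**What to change.** Make the arm comparison per participant over all randomised patients. For each participant, count polyps (and adenomas) in each size, location, morphology and histology class, with zeros for patients in whom none was found. Compare arms with a count model, for example negative binomial with robust standard errors, adjusted for the stratification factors (age category, sex, site, referral category). The model has to be specified for this purpose: the article analyses MAP by ANOVA, so there is no existing count model to reuse. This also fits the rule that all randomised patients are included, and it shows directly whether extra polyps are small ones or whether counts of large ones change.

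If the per-polyp multinomial or ANOVA comparison is kept, state the unit, use patient-clustered robust standard errors or a patient random effect, and label the result descriptive and conditional on detection.

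The cost is SAP wording and a few more lines of code. The features are already recorded per polyp, so no new data are needed.
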